##### Session structure

The structure of the sessions will be:AWarm-up

The warm-up will entail cycling at a frequency between 60 and 70 revolutions per minute. This will be performed on an electromagnetic cycle ergometer (Ergoline Viasprint150p). The initial session will be conducted with a 60-W resistance load. Subsequently, individual adjustments in the watt resistance will be made in order to achieve a moderate activity level (a score of 4–5 on a 0 to 10 scale) on a validated OMNI scale specific to cycle ergometer [33]. Consequently, in the event that a participant indicates a score of less than 4 on the OMNI scale, the resistance will be increased by 5 W in the next session.

BWBV training

The WBV will be performed on a synchronous vertical vibration platform (Power Plate® Pro5; PowerPlate, Amsterdam, The Netherlands) with the participant positioned barefoot and with a contoured mat provided by Power Plate®. The WBV protocol is presented in Table 1. The protocol details for months 1–4 can be found in Supplementary Tables 3, 4, 5, and 6, respectively. Prior to commencing the WBV session, the supervisor will provide an explanation of the exercises to be performed during the session. All exercises will be performed with both the forefoot and the heel touching the platform, with the exception of calf raises and bent knee calf raises, which will be performed without contact of the heel with the platform. In order to prevent skidding on the mat provided by the Power Plate, participants will wear socks. As specified in Fig. 2, all exercises will be performed with flexion of at least one lower limb joint in order to prevent vibrations from being transmitted to the head. At the beginning of each month, novel exercises will be introduced, and participants will be allowed to grasp the WBV platform handrail with both hands in order to perform the exercises during the first week. In the subsequent week, participants will be instructed to perform the exercise with one hand only. Over the course of the final weeks of each month, they will be encouraged to progress to a position where they are able to perform the exercises without holding on to the handrail, as detailed in Supplementary Tables 3, 4, 5, and 6. It is important to note that no dumbbells or resistance bands will be utilized during the performance of exercises on the Power Plate®.

**Table 1 Tab1:** WBV protocol

Week	Warm-up (min)	WBV exercises (repetitions) [duration (s)]	Rest (s)	Freq. (Hz)	Ptp Disp. (mm)	Complimentary exercises^b^	Session duration (min)^d^
1	6	Half squat (× 10) [20 s]	60	30	1	(A, B, C, D) × 1 set × 12 reps	28
2	6	Half squat (× 15) [20 s]	60	30	1	(A, B, C, D) × 2 sets × 12 reps	43
3	8	Half squat (× 12) [20 s]	60^a^	30	1	(A, B, C, D, E, F, G, H) × 3 sets × 12 reps	40
		Calf raises (× 12) [20 s]	60^a^	30	1		
4	8	Half squat (× 10) [30 s]	60^a^	30	1	(A, B, C, D, E, F, G, H) × 3 sets × 12 reps	38
		Calf raises (× 10) [30 s]	60^a^	30	1		
5	10	90° squat (× 10) [30 s]	60^a^	30	1	(A, B, C, D, E, F, G, H) × 3 sets × 12 reps	40
		Calf raises (× 10) [30 s]	60^a^	30	1		
6	10	90° squat (× 10) [30 s]	60^a^	30	1	(A, B, C, D, E, F, G, H) × 3 sets × 12 reps	46
		Calf raises (× 10) [30 s]	60^a^	30	1		
7	10	90° squat (× 10) [30 s]	30	30	1	(G) × 5 sets × 12 reps	42
		Calf raises (× 10) [30 s]	30	30	1		
		Glute bridge (× 5) [15 s]	45	30	1		
8	10	90° squat (× 12) [30 s]	30	30	1	(G) × 2 sets × 12 reps (V) × 2 sets × 15 s (VII) × 3 sets × 15 s	48
		Calf raises (× 12) [30 s]	30	30	1		
		Glute bridge (× 5) [15 s]	45	30	1		
9	10	Split squat (× 10) [30 s]	30	30	1	–	42
		BN calf raises (× 10) [30 s]	30	30	1		
		Kneeling push up (× 4) [15 s]	45	30	1		
		Glute bridge (× 6) [30]	30	30	1		
10	10	Split squat (× 11) [30 s]	30	35	1	(VIII) × 1 set × 10 s	45
		BN calf raises (× 11) [30 s]	30	35	1		
		Kneeling push up (× 4) [30 s]	30	30	1		
		Glute bridge (× 6) [30]	30	30	1		
11	10	Split squat (× 10) [30 s]	30	35	1	–	42
		Plank (× 2) [15 s]	45	30	1		
		BN calf raises (× 10) [30 s]	30	35	1		
		Kneeling push up (× 3) [30 s]	30	30	1		
		Glute bridge (× 5) [30 s]	30	30	1		
12	10	Split squat (× 7) [45 s]	15	35	1	(X) × 2 sets × 10 reps	38
		Plank (× 3) [15 s]	45	30	1		
		BN calf raises (× 7) [45 s]	15	35	1		
		Kneeling push up (× 4) [30 s]	30	30	1		
		Glute bridge (× 5) [30 s]	30	30	1		
13	10	Dynamic squat (× 9) [45 s]	15	30	2	–	39
		Plank (× 4) [15 s]	45	30	1		
		Step lunge (× 5) [30 s]	30	30	1		
		Kneeling push up^c^ (× 4) [15 s]	45	30	1		
		Glute bridge (× 5) [30 s]	30	30	1		
14	10	Dynamic squat (× 10) [45 s]	15	30	2	–	42
		Plank (× 4) [20 s]	40	30	1		
		Step lunge (× 6) [30 s]	30	30	1		
		Kneeling push up^c^ (× 4) [20 s]	40	30	1		
		Glute bridge (× 6) [30 s]	30	30	1		
15	10	Dynamic squat (× 11) [45 s]	15	30	2	–	45
		Plank (× 4) [20 s]	40	30	1		
		Step lunge (× 7) [45 s]	15	30	1		
		Push-ups (× 5) [20 s]	40	30	1		
		Glute bridge (× 6) [30 s]	30	30	1		
16	10	Dynamic squat (× 11) [45 s]	15	30	2	–	45
		Plank (× 4) [20 s]	40	30	1		
		Step lunge (× 7) [45 s]	15	30	1		
		Push-ups (× 5) [20 s]	40	30	1		
		Glute bridge (× 6) [45 s]	15	30	1		

^a^Active rest (elastic band exercises during the rest); ^b^Complimentary exercises explained in Fig. 2; ^c^Feet on a step that is the same height as the WBV so that the push-ups are performed totally horizontal; ^d^Includes a 2-min rest between the warm-up and the beginning of the WBV training; *BN*, bent knee; *Freq.*, frequency; *Ptp Disp.*, peak to peak displacement

**Fig. 2 Fig2:**
[figure not shown]
Elastic band and WBV exercises. Exercise X is an exercise that starts with the participant standing on a step and advancing one leg to step on the WBV platform finishing in split squat position (exercise V) to then go back to standing up on the step and repeating with the other leg. Exercise XI is a dynamic squat from 120 to 90°

As illustrated in Table 1, complementary exercises will be conducted during the initial 6-week period and are elucidated in detail in Fig. 2 and in the “Elastic band training” subsection described below. During certain weeks, the complementary exercises will be performed on the WBV platform without the device being activated as a means of familiarization, while in the following weeks, the same exercises will be performed with the vibration stimulus.C.Elastic band training

The initial 6-week phase of the WBV training program will be accompanied by an elastic band training component. All exercises will be performed at a speed of 2 s for the concentric phase and 2 s for the eccentric phase. The exercises will be performed using Thera-bands (Thera-Band, Hadamar, Germany). Participants will start with the yellow band and perform the exercises until they reach approximately a 200% elongation at the conclusion of the concentric phase. As participants progress, they will increase the intensity of the exercises using different colors of bands. The tension generated by each band at a 200% elongation is as follows: yellow (1.69 kg-force (kgF)), red (2.26 kgF), green (2.91 kgF), blue (3.52 kgF), black (5.23 kgF), silver (5.91 kgF), and gold (7.55 kgF) [36]. At the conclusion of the final circuit of the day, a visual scale designed for Thera-Band bands [35] will be employed. Should participants indicate a perception below 5 (“somewhat hard”) on a scale of 10, a harder band will be used in the next session.

During the first week, the exercises will be performed after the WBV training. Participants will perform a circuit of four exercises (chest fly, biceps curl, row, and triceps kickback (Fig. 2)) with 12 repetitions per exercise and a 1-min rest interval between each exercise. The circuit will be repeated twice during the second week. The first repetition will be performed after the fifth WBV repetition and the second after the tenth WBV repetition: 5 WBV repetitions, circuit (4 exercises * 12 reps), 5 WBV repetitions, circuit (4 exercises * 12 reps), 5 WBV repetitions.

During the third week, four new exercises will be introduced including pull apart, horizontal woodchopper, wall push-ups, and straight arm pull down (Fig. 2). From week 3 to week 6, the same circuit will be performed three times with 12 repetitions per exercise.

The exercises will be incorporated into the remaining WBV repetitions. This will result in an active rest period of approximately 1 min between the vibration stimulus (the time that participants take to do the elastic band exercises).

##### Training frequency, intensity, and duration

Those allocated to the WBV group will attend three weekly supervised sessions for 16 weeks, with a total of 47 sessions completed (during the first week, only two sessions are performed). Participants will be permitted to select the time of day and day of the week for each session, provided that a minimum of 24 h elapsed between each session and that the training is not performed on three consecutive days.

The duration of the sessions will range from 28 to 46 min, with the intensity increasing weekly through an increase in the number of repetitions, time of vibration, or reduction in rest times as illustrated in Table 1.

In the WBV, all participants will receive the same stimulus, resulting in varying internal loads for each individual. Nevertheless, for the warm-up and the elastic band training, the resistances will be adjusted as previously explained in order to achieve a similar internal load for all participants.

##### Whole-body vibration device

Supplementary Table 7 presents all the information regarding the vibration device that will be used in the present study in accordance with the “*Reporting Guidelines for Whole-Body Vibration Studies in Humans, Animals and Cell Cultures: A Consensus Statement from an International Group of Experts*” guidelines [37]. The specific device presents a constant frequency and magnitude and the vibration parameters have been previously tested in our laboratory [38].

### Outcome variables

The primary outcomes will be (1) body composition, (2) results obtained from the adapted Bruce protocol, (3) basal metabolic rate, and (4) perceived quality of life. All the other variables will be considered as secondary variables. Both primary and secondary outcomes are explained in detail below.

All tests will be conducted in the GENUD-Lab, with the exception of the blood and stool collection, which will be performed at Clinico Lozano Blesa Hospital (situated a 5-min walk from the GENUD-Lab). The outcome variables will be assessed at four different time points (see Fig. 1 or 3). In each time point, participants will attend the laboratory on two different days, with less than a week between them. On each day, different variables will be collected, as detailed below.

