#### Exercise program rationale

The main aim of the current exercise program is to reduce the loss of bone and lean mass that is commonly observed after BS. Maintaining lean mass is crucial as it helps to preserve the basal metabolic rate, which often declines after BS [29], and may negatively affect body mass loss and body mass maintenance in the long run. Avoiding the loss of lean mass will lead to the preservation of muscle strength, enabling individuals to engage in more intense physical activity and improve their quality of life. Moreover, it is possible that an exercise intervention may also have a positive effect on cardiovascular markers and the gut microbiota.

High-impact exercises that involve jumping and high-speed changes of direction have been demonstrated to be the most effective in improving bone mass [30]. However, these exercises are contraindicated for individuals with obesity, as the additional weight they carry can cause adverse effects on the joints. This is due to the high forces generated during these activities. Therefore, an alternative intervention that has demonstrated efficacy in enhancing bone and lean mass, reducing fat mass, and improving some cardiometabolic markers is training with WBV platforms. A review conducted by Zago et al., which included 18 studies with obese patients, demonstrated that WBV training can improve bone and lean mass [31].

A 16-week training program was selected based on a previous study that included a large number of clinical trials, which found positive effects of exercise interventions that lasted more than 3 months [32]. A 16-week intervention was deemed appropriate, given that bone adaptation requires a longer period than that of lean and fat mass. Although the present protocol includes elastic band training, which could also mask the WBV results, this type of training is only performed for the first 6 weeks. Its purpose is to improve muscle strength in the upper limbs and core, in order to work them out in the next 10 weeks with the WBV platform.

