##### Body composition

A Hologic Horizon QDR dual energy X-ray absorptiometry (DXA) scanner (Hologic Inc, Bedford, MA) will be used to perform whole-body, hip, and lumbar spine scans. The left hip will be measured in all participants. The three scans will yield areal BMD (aBMD, g/cm^2^), bone mineral content (BMC, g), and bone area (cm^2^). The Horizon QDR series enables for a whole-body scan in patients with morbid obesity as the arm and/or leg can be placed outside the scanning area (due to the size limitations of the DXA device, it may not be possible to scan the entire body of large patients). The software will then copy the complete scanned arm or leg to the arm or leg with missing information. In addition to the assessment of aBMD, BMC, and bone area, the whole-body scan will also yield data on lean and fat mass (in grams) and visceral adipose tissue (area in cm^2^, volume in cm^3^, and mass in grams) from the whole-body scan. The trabecular bone score will also be determined using the Hologic-specific software (TBS Hologic).

The bone structure, strength indexes, and BMC of the non-dominant forearm will be measured using a peripheral quantitative computed tomography (pQCT) using a Stratec XCT-2000 L pQCT scanner (Stratec Medizintechnik, Pforzheim, Germany). The forearm will be measured at 4% of the total length to evaluate trabecular bone and at 66% of the total length to evaluate cortical bone. The coefficients of variation for the pQCT in our laboratory have been published elsewhere [39].

Although the International Society of Clinical Densitometry recommends bone scans to be performed with a year difference when a new treatment has begun (in our case the exercise treatment), they also state that in conditions associated with rapid bone loss, testing more frequently is appropriate [40]. It has been demonstrated that BS has a detrimental effect on bone loss, particularly in the initial year following surgery [16]. Previous studies have indicated that significant bone loss can occur as early as 6 months post-surgery [41].

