### Statistical methods

The Shapiro–Wilk test will be used to test for normality of the data while variance homogeneity and sphericity will be assessed with the Levene and Mauchly tests, respectively. To assess changes over time in the assessed outcomes, a repeated-measures ANOVA with Bonferroni correction will be used to assess the interaction between group (control group vs. WBV) and time (baseline vs. 2nd vs. 3rd vs. 4th assessments). In the absence of a normal distribution, data will be analyzed with the Wilcoxon test for within-group comparisons and the Mann–Whitney test for between-group comparisons using Bonferroni’s correction. To test for associations between variables, both correlations and linear regressions will be performed. The significance level will be set at 5%. Per-protocol and intention-to-treat analyses will be performed in order to account for the possible dropouts during the study. In the per-protocol analysis, we will include only the participants who attend at least 70% of the sessions and undergo the baseline and post-intervention outcome assessments. For the intention-to-treat analysis, we will consider all the participants who will undergo the baseline assessments and subsequently participate in at least one additional assessment following their group assignment will be considered.

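### Four whole domains are primary with no variable or time point fixed, so the plan either leaves error across them uncontrolled or lacks its stated 80% power

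*Protocol article*

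**What the plan says.** Under Outcome variables, the protocol article says: "The primary outcomes will be (1) body composition, (2) results obtained from the adapted Bruce protocol, (3) basal metabolic rate", and adds perceived quality of life as the fourth. Everything else is secondary. The section promises detail on the outcomes further on. That detail lists what each test yields and does not choose among the results.

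Statistical methods specifies that "a repeated-measures ANOVA with Bonferroni correction will be used to assess the interaction between group (control group vs. WBV) and time". For non-normal data it names "the Mann–Whitney test for between-group comparisons using Bonferroni’s correction". It then states "The significance level will be set at 5" per cent. Neither mention of Bonferroni says which set of tests it covers.

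Sample size powers one within-between interaction test (two groups, four measurements) at 5% and 80% power, giving 12 per group, 24 in all, raised to 28 for attrition.

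Exercise program rationale states a narrower purpose: "The main aim of the current exercise program is to reduce the loss of bone and lean mass" seen after bariatric surgery.

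**The concern.** A superiority trial needs a fixed variable on which superiority is judged. Here the primary outcome is a choice among many variables, and no rule is given for how a result on one of them counts. If one primary variable crosses 0.05 and the others do not, nothing in the text stops the superiority claim from resting on that one. The abstract expects results proving the training effective and safe, and the Discussion looks ahead to including it in usual care, so a claim resting on one favourable variable would matter.

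The sample size makes no allowance for several primary tests. Either the error rate across the primary variables is not held at 5%, or it is held and the stated power no longer applies.

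**Working it through.** **1. Count of primary variables, from the article's own sections**
- Body composition, DXA: 3 scans × 3 bone measures = 9; lean and fat mass = 2; visceral fat (area, volume, mass) = 3; trabecular bone score = 1. Sum 15.
- Body composition, pQCT: structure, strength and mineral content at two forearm sites; the number is not given.
- Modified Bruce protocol: peak oxygen uptake and anaerobic threshold = 2.
- Resting metabolic rate: 1, if its other listed outputs are ignored.
- Quality of life: EQ-5D-5L, 5 dimensions + visual analogue scale = 6; SF-36 = 8. Sum 14.

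Total 15 + 2 + 1 + 14 = 32 before any pQCT variable. Bioimpedance, under Anthropometric data, gives a second measure of fat mass. I use 30 as a round figure.

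**2. The plan's own sample size**
- Inputs: partial eta squared 0.06, correlation 0.5, 4 measurements, 2 groups, alpha 0.05; sphericity assumed.
- f² = 0.06/0.94 = 0.0638.
- λ = f² × N × 4/(1 − 0.5) = 0.0638 × 24 × 8 = 12.26 at N = 24.
- Degrees of freedom: 3 and 3 × (24 − 2) = 66.
- Power from the noncentral F: 82.5% at N = 24 and 78.4% at N = 22.

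The stated 24 is reproduced with one test at an undivided 5%.

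**3. If each primary variable is tested at 5%**

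Under independence, the chance of at least one false positive is 1 − 0.95^K:
- K = 4: 18.5%
- K = 15: 53.7%
- K = 30: 78.5%
- K = 32: 80.6%

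The article gives no correlations between outcomes, so I simulated the interaction F test with no true effect (N = 24, four times, correlation 0.5 over time, 4,000 runs per row). The 30 variables were split 16, 2, 1 and 11 over the domains. The last column counts only false positives whose T1-to-T3 change favours vibration training.

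| Assumed correlation within / between domains | Any false positive | Favouring vibration |
|---|---|---|
| 0 / 0 | 79% | 53% |
| 0.3 / 0.1 | 72% | 45% |
| 0.5 / 0.2 | 63% | 38% |
| 0.7 / 0.2 | 51% | 30% |
| 0.8 / 0.3 | 42% | 23% |
| 0.9 / 0.3 | 33% | 20% |

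With one variable per domain, the simulated figure for any false positive stays at about 17% to 18% throughout.

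**4. If Bonferroni covers the primary variables**

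Same F test with a smaller alpha:
- Four variables, 0.05/4 = 0.0125: power 64% at N = 24 and 74% at N = 28; about 32 analysed needed for 80%.
- Thirty variables, 0.05/30 = 0.00167: power 38% at N = 24 and 49% at N = 28; about 44 analysed needed.

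Even with no dropout, the 28 recruited do not reach 80% in either case.

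**The case against.** The best defence is that a Bonferroni correction is named twice, so a reader who infers that every primary variable is tested at a plain 5% goes beyond the text. That stands: the scope is unstated. The wording attaches the correction to the group-by-time analysis and the non-parametric comparisons, and the sample size uses an undivided 5%. Both suggest contrasts within one outcome, but neither establishes it. The defence does not rescue the plan, because the wider reading removes the stated power (step 4).

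A reader might also infer that a false claim of effectiveness is likely. The documents do not support that. The 79% assumes independence, which the body composition measures rule out: areal density, mineral content and bone area come from the same scan and are linked by their units, and three visceral-fat figures describe one tissue. A false claim of benefit must also favour the intervention, and that chance passes 50% only near independence.

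The count is an order of magnitude, since the pQCT variables are not enumerated and Objectives glosses body composition simply as bone, fat and lean mass. Nor is it right that the trial has no defined test: the group-by-time interaction is defined. The variable and the family of tests are not.

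A multiplicity rule may sit in an analysis plan not shown, so its absence alone is no finding. Which variable is primary is the protocol's to fix, and the sample size printed here leaves no room for such a rule.

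**Conclusion.** The point holds in this form: no primary variable or time point is fixed, the scope of the Bonferroni correction is unstated, and no control across primary variables is described. With about 30 variables each at 5%, the chance of at least one false positive is 79% under independence and about 33% to 72% under the correlations assumed here. In favour of vibration training it is about 20% to 53%. Even the lowest figure is about four times 5%. If the correction does cover the primary variables, power at 24 analysed is about 38% for thirty or 64% for four, against the stated 80%.

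The power figures rest on the plan's own inputs and on sphericity. The error figures rest on the count of about 30 and on correlations that the documents do not give. It should be settled before results are known.

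**What to change.** Name one primary variable and one time point taken from the stated main aim, a bone or a lean mass measure, and keep the 5% level for it. Make everything else secondary, reported with estimates and confidence intervals and no confirmatory claim.

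If four domains must stay primary, name one variable and time point in each, apply Holm across the four, and restate power as about 64% at alpha 0.0125 with 24 analysed. In either case, say in Statistical methods what the Bonferroni correction covers.

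The 82% and 64% belong to the four-time interaction test. If the primary test becomes a comparison at one time point, power must be recomputed for that test, because it depends on when the effect appears and the plan does not say.

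Cost: a protocol amendment with the ethics approval that the article requires for changes, any matching registry update, and a less favourable stated power if four primaries are kept.
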